### Participants and recruitment

Adult patients who are undergoing surgery for a degenerative condition of the lumbar spine (lumbar spinal stenosis, spondylolisthesis or degenerative disc disease) using any kind of surgical decompression (laminectomy, hemilaminectomy, foraminotomy, with open or minimally invasive technique) associated with fusion, and able to read and speak Italian (site in southern Switzerland) or Dutch (site in the Netherlands) will be eligible for inclusion. One hundred and fifty patients will be enrolled at the outpatient clinic of the Department of Neurosurgery, Neurocenter of Southern Switzerland, Regional Hospital of Lugano, Lugano, Switzerland (Site 1) and the Department of Neurosurgery of Zuyderland Medical Center, Heerlen, The Netherlands (Site 2). All patients entering the screening phase will be registered on a Patient Registration Log and a unique registration number will be assigned. Clinical data will be assessed to evaluate a subject’s eligibility.

Patients will be excluded from the study if they meet any of the following criteria:
Plans to undergo major surgery within six months after current lumbar spinal fusion surgeryComorbid severe psychiatric conditions such as schizophrenia or personality disorderKnown or suspected non-compliance, drug or alcohol abuseInability to follow the procedures of the study, e.g. due to dementiaThe presence of any serious medical comorbidity such as sepsis or cancer that might cause disability or worsen the patient’s general health conditionPregnancyAn opioid intrathecal pumpPrisoners

Patients eligible for participation will be evaluated at least 6 weeks before surgery and asked for informed consent, and then to complete the PCS [23]. Patients with high pain catastrophizing, defined as a score of ≥24 on the PCS, will be eligible for randomization to perioperative treatment with CBT or educational program. This cut-off was initially based on a previous study in whiplash patients that showed that a pretreatment score of 24 or higher on the PCS best predicted follow-up pain ratings and work status after multidisciplinary treatment [24]. More recently, Tuna et al. [16] suggested an almost identical cut-off for the PCS (i.e. > 24) to obtain the highest sensitivity and specificity to predict unfavorable outcome after spine surgery, defined by as score on the Oswestry Disability Index (ODI) of 20 or higher.

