A non-randomized group, consisting of low catastrophizing patients (score < 24 PCS), will be included as an observational cohort. These patients will not undergo any additional intervention besides usual care but will undergo the same data-collection as the high catastrophizing randomized groups.

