#### Secondary outcomes

Secondary outcomes are leg/back pain, disability, quality of life, depression, patient’s global impression of change, pain catastrophizing, pain medication regimen, and work productivity and activity impairment. These will be measured using the following questionnaires:
Numeric Rating Scale (NRS) for back and leg pain. Pain intensity is assessed on an 11-point scale ranging from 0 (no pain at all) to 10 (the worst imaginable pain) [31].Oswestry Disability Index (ODI): a self-administered questionnaire, assessing a patient’s limitations in activities of daily living. The ODI has ten questions scored on a 6-point scale. The total score ranges from 0 to 100, with higher scores denoting higher functional disability [32].European Quality of Life Five Dimension Five Level Scale (EQ-5D-5L): This questionnaire assesses health related quality of life in terms of five dimensions: mobility, self-care, usual activities, pain/discomfort, and anxiety/depression [33]. Each of the 5 items are scored on a 5-point scale, ranging from no problems in that domain to extremely problematic.Depression is measured by the PROMIS (Patient-Reported Outcomes Measurement Information System) Short Form v1.0 - Depression 8b [34]. The eight questions are scored from 0 to 5. Higher scores denote higher levels of depression.Patient’s Global Impression of Change (PGIC): This scale assesses patient’s own assessment improvement or deterioration over time on a 7-point scale (1. very much improved - 7. very much worse).Pain Catastrophizing Scale (PCS): The PCS is a 13-item scale that measures catastrophic thinking in relation to pain. Each item is scored on a 5-point scale ranging from 0 (never) to 4 (always) [23]. Higher scores denote higher levels of catastrophizing. Psychometric properties of the PCS have been studied extensively in a variety of patient populations having painful disorders and found to be good to excellent [35, 36]. In addition, the PCS has been shown to be sensitive to psychosocial interventions designed to increase the use of adaptive coping strategies and decrease the use of maladaptive coping strategies, such as pain catastrophizing [37].Medication Quantification Scale (MQS): The MQS is an instrument or quantifying medication regimen use in chronic pain populations. The score is calculated for each medication by taking a consensus-based detriment weight for a given pharmacologic class and multiplying it by a score for dosage. The calculated values for each medication are then summed for a total MQS score. The score can provide a useful point measure of medication usage for any pain medication regimen [38, 39].Work productivity and activity impairment will be assessed using the Work Productivity and Activity Impairment questionnaire: Low Back Pain (WPAI:LBP) [40]. This questionnaire measures the effect of the specific health problem ‘low back pain’ on work productivity and activity impairment. Specific outcomes are absenteeism (work time missed), presenteeism (impairment while working), overall work impairment (absenteeism plus presenteeism), and activity impairment (impairment in regular activities) due to LBP. Each score is represented as a percentage, and higher scores indicate less productivity or greater impairment.

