All patients randomized (i.e. those with a PCS score > 24) will be analyzed in an intention-to-treat analysis. To test for a difference between the CBT and control group in the COMI at 12 months, linear regression will be used, with correction for baseline COMI and center. In addition, the difference in the trajectory of COMI over time will be assessed by means of linear mixed-effects regression, taking all follow-up measurements into account. Adjustment for center, type of surgery, age and gender will be made and, if necessary, for other prognostic variables significantly associated with the outcome (i.e., acute postoperative pain intensity, severity of catastrophizing, preoperative depression, preoperative surgical fear, length of current sick leave, pain duration). Stepwise backward elimination using the Wald test will be used to select prognostic variables significantly associated with the outcome. Any control variables that are incomplete will be imputed if the proportion of incomplete patients exceeds 0.05. We will use multiple imputation with fully conditional specification with the number of imputations set to the percentage of incomplete patients. Predictive mean matching will be used to draw values to be imputed. Secondary outcome variables will be analyzed similar to the primary outcome. For these, logistic regression analysis adjusted for center will be used to test for differences in proportions at 12 months postoperatively.

Exploratory, we will compare the outcomes of the patients in the two intervention groups with the outcomes of patients with low pain catastrophizing scores (i.e. those with a PCS score < 24) undergoing care as usual. Linear mixed-effects regression for the three groups will be performed with primary and secondary outcomes at the three postoperative assessment periods and controlling for preoperative values. This analysis will indicate whether high catastrophizing patients follow a similar trajectory of pain and functioning after spinal fusion surgery compared non-catastrophizing patients.

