It should be noted that none of the above studies preselected patients based on a psychological high-risk profile (i.e. high pain catastrophizing or anxiety/fear) despite the fact that at least some of these interventions were specifically designed to reduce these risk factors. Lotzke et al. speculated that their null finding may have been due to the high degree of variability in fear-avoidance beliefs in their patients [59]. Therefore, they recommended that future studies should evaluate the effects of psychological treatment specifically in patients with a high psychological risk profile for poor outcome.

In line with this recommendation, a crucial aspect of the current study is that we will offer CBT specifically to patients reporting high levels of pain catastrophizing. Another feature, which sets out study protocol apart from most previous studies in this area, is the inclusion of an active control intervention consisting of an educational and progressive exercising program. This allows us to assess the effect of CBT per se and control for non-specific effects such as expectancy, contact time and attention. In addition, starting treatment before surgery may be expected to lead to more profound intervention effects than post-surgical intervention only, because it might decrease early postoperative pain, which is among the most prominent predictive factors for developing CPSP [60]. Finally, we aim to assess the meaningfulness and clinical usefulness of the perioperative CBT intervention by comparing the outcomes of the high PCS/CBT group not only with the control group, but also to the outcomes of the low risk group (i.e. PCS score < 24). This offers the possibility to examine whether CBT can reduce the negative effects of catastrophizing on outcome to the level of improvement one would expect in non-catastrophizing patients.

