Furthermore, this study can demonstrate efficacy of the CBT intervention for high catastrophizing patients, but it does not assess cost-effectiveness. Although some cost elements are included (medication use, further treatment, employment status), no full cost analyses will be conducted. Moreover, if this study shows a positive effect on pain and disability from perioperative CBT, this will not clarify the optimal dosage of the intervention or the ideal timing. Finally, it cannot clarify whether a PCS score of 24 or higher is the most optimal cut-off for offering patients CBT. Future studies should conduct sensitivity analyses to establish at which level of pain catastrophizing intervention should be offered, to come to an optimal cost-benefit ratio.

In conclusion, the results of this study are expected to provide valuable information that will potentially change clinical practice of lumbar spinal fusion surgery. If our study can demonstrate that perioperative CBT is effective in improving clinical outcome after lumbar spine fusion surgery in high catastrophizing patients, it is highly recommended to perform prescreening to identify this subgroup for which a perioperative psychological treatment will be indicated. If CBT will not prove to be superior and if this study will confirm that high levels of pain catastrophizing have a negative impact on clinical outcome, that might be a reason to be very reluctant in offering these patients a spinal fusion procedure, trying to opt for less invasive treatment options.

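### The exploratory high-versus-low catastrophizing model compares patients with equal preoperative scores, while the stated question is whether the groups improve alike; for the PCS itself the adjusted contrast is extrapolation

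*Protocol article*

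**What the plan says.** Under Participants and recruitment, high catastrophizing is "defined as a score of ≥24 on the PCS", and "low catastrophizing patients (score < 24 PCS), will be included as an observational cohort". The low group receives usual care only; both randomised groups receive an additional program.

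Under Power considerations and statistical analysis, the comparison with the low group is introduced as "Exploratory, we will compare the outcomes of the patients in the two intervention groups" against those low-scoring patients. The method is a linear mixed-effects regression for three groups "with primary and secondary outcomes at the three postoperative assessment periods and controlling for preoperative values". The section then says what the model will deliver: "This analysis will indicate whether high catastrophizing patients follow a similar trajectory of pain and functioning after spinal fusion surgery".

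The Discussion words the aim as finding out whether CBT can bring high catastrophizers "to the level of improvement one would expect in non-catastrophizing patients". Its closing paragraph makes a conditional remark about offering fusion surgery if CBT is not superior and "if this study will confirm that high levels of pain catastrophizing have a negative impact on clinical outcome".

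The list of secondary outcomes includes the grouping score: "global impression of change, pain catastrophizing, pain medication regimen". The Background reports that catastrophizing goes with more pain and disability in lumbar stenosis. No margin for similarity is given.

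**The concern.** Between randomised arms, adjusting for baseline and comparing change aim at the same effect, because expected baselines are equal. Here one group is a separate cohort selected on a preoperative score that is expected to go with preoperative pain and disability. The two analyses then answer different questions and can disagree (Lord's paradox). Conditioning on baseline matches high catastrophizers who have relatively mild symptoms with low catastrophizers who have relatively severe ones. It does not estimate how much each group improved.

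At stake is how the low-PCS cohort may be used. The Discussion relies on it to judge the clinical usefulness of CBT, and it is the only low-catastrophizing comparator for a statement about the effect of catastrophizing on outcome.

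**Working it through.** **The plan's own figure.** A difference of 2 COMI points, SD 2.5, two-sided 0.05 (sidedness assumed) and power 0.95 require 41.6, so 42, per group by the t-test; power at 42 is 0.952. With 15% dropout, 42/0.85 = 49.4, so 50 per group and 150 over three groups. The figures reproduce and are not in dispute.

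**What each contrast estimates.** At one postoperative visit, let D be the preoperative mean difference (high minus low), P the postoperative mean difference, and b the common within-group slope of postoperative on preoperative score.

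- Baseline-adjusted contrast: A = P - b x D
- Contrast in change: C = P - D
- Hence A - C = (1 - b) x D

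The two agree only if D = 0 or b = 1. If both groups improve equally (C = 0), the adjusted contrast is (1 - b) x D, and the high group looks worse because higher COMI is worse.

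**Size.** The article gives neither D nor b, so both are assumed:

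| Gap D (COMI points) | b = 0.3 | b = 0.5 | b = 0.7 |
|---|---|---|---|
| 0.5 | 0.35 | 0.25 | 0.15 |
| 1.0 | 0.70 | 0.50 | 0.30 |
| 1.5 | 1.05 | 0.75 | 0.45 |

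A simulation agrees with the formula (42 against 42 patients, PCS cut at 24, equal mean improvement; assumed COMI SD 2.5 and PCS-COMI correlation 0.3): a gap of 1.14 with slope 0.5 gave an adjusted difference of 0.57 = 0.5 x 1.14.

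**Change is not automatically right either.** Suppose the preoperative gap is wholly transient, so that the groups end at the same level (P = 0). Then C = -D and A = -b x D. With D = 1 and b = 0.5, change shows -1.0 and the adjusted model -0.5. Both carry regression to the mean, and change carries more.

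**PCS as outcome.** The preoperative value is now the variable that defines the groups: every low patient is below 24 and every high patient at or above it. No baseline value occurs in both groups, so the group coefficient depends wholly on the fitted line being correct where one group has no data. This needs no assumed figure.

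**Similarity.** For change, SD = 2.5 x sqrt(2(1 - r)) if 2.5 is the SD at each visit and r the pre-post correlation. With 42 per group, the 95% half-width is 1.989 x SD x sqrt(2/42):

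| r (assumed) | SD of change | Half-width | Chance that the CI lies within ±2 if the true difference is 0 |
|---|---|---|---|
| 0.3 | 2.96 | 1.28 | 0.73 |
| 0.5 | 2.50 | 1.09 | 0.91 |
| 0.7 | 1.94 | 0.84 | 0.99 |

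The ±2 is only an illustration, taken from the trial's clinically meaningful difference. At r = 0.3 or 0.5 an interval of this width cannot fit inside ±1. What similar means thus depends on a margin that the article does not state.

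**The case against.** The strongest defence is that the adjusted contrast is a legitimate estimand. The article also speaks of comparing outcomes, and asking whether patients with equal preoperative COMI reach equal postoperative COMI is a sensible question. For COMI, ODI and NRS the baseline ranges can overlap, and group-by-time terms, if included, would compare the postoperative course. This stands. It is why the adjusted model should be kept and why the figures above are a gap between two questions, not an error in one of them.

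It is also fair that the size rests on assumed inputs, that change scores have their own regression to the mean, and that the comparison is labelled exploratory on an observational cohort. Margins and model terms for such an analysis are often left to the analysis plan.

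Two parts are not answered. The article itself says that this model will indicate similar trajectories and names improvement as the target, so the mismatch lies in its own text. And the lack of overlap for PCS follows from the group definitions. The interpretive sentence mentions pain and functioning only, but the model is specified for all secondary outcomes, which include PCS.

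**Conclusion.** The point holds in limited form. The specified model estimates a conditional contrast that differs from the stated target whenever preoperative levels differ, as the Background suggests they will. For COMI the discrepancy is 0.15 to 1.05 points under the assumed gaps and slopes; the true value cannot be fixed from the article. For PCS the adjusted contrast is extrapolation.

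Three stronger readings are tempting and not supported:

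- That the model cannot inform about trajectories at all. For outcomes other than PCS it gives an interpretable conditional comparison.
- That any adjusted difference would be a false effect. That presupposes equal true improvement, which nobody knows.
- That the trial will read a non-significant result as similarity, or will advise against surgery on this comparison. The article states no such decision rule, and the closing remark in the Discussion is doubly conditional, cautiously worded and tied to no particular analysis.

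What can be said is that both high-PCS arms receive a program that the low cohort does not, so this comparison alone cannot isolate the effect of catastrophizing. Severity is minor; the randomised primary analysis is untouched.

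**What to change.** 1. Keep the baseline-adjusted three-group model for outcomes other than PCS.
2. Report beside it a mixed model with the preoperative value as one of the repeated outcomes, free group means at baseline and group-by-time terms. Give group differences in level and in change at 2, 6 and 12 months with 95% CIs.
3. State that the two models answer different questions and that neither is free of regression to the mean.
4. Show PCS by group descriptively, without baseline adjustment.
5. Base any statement of similarity on the confidence interval against a margin chosen and justified in advance, not on a non-significant difference.
6. State that both high-PCS arms received a program which the low-PCS cohort did not, and that this comparison alone cannot isolate the effect of catastrophizing or carry the closing inference in the Discussion.

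The cost is a little more analysis and a narrower exploratory conclusion. No new data are needed, and the sample size and primary analysis do not change.

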## Discussion

Over the past 15 years, an increase in the number of spinal fusion procedures for degenerative diseases has been observed. A recent analysis on a large national database [45] reported a 62% increase in volume of these procedures from 2004 to 2015. This could reflect an aging population, but also an improvement in the diagnostic process, intraoperative technologies (like spinal navigation) and perioperative care of these patients. However, while a clear benefit in terms of pain, disability and return to work has been shown in patients suffering from spinal instability [46–48], recent RCT’s [47, 49] have questioned the usefulness of spinal fusion procedures for other conditions like spinal stenosis or degenerative spondylolisthesis. As a matter of fact, in many situations and in many health systems, decision-making regarding indications for spinal fusion is driven by surgeons’ and patients’ preferences, hospital factors and reimbursement policies [45, 50].

Controversies about indications for spinal fusion pose specific problems since these patients are at risk for CPSP, which has a significant impact on patient’s quality of life and can even lead to new-onset psychiatric diseases [51]. The biopsychosocial model views pain as the result of the dynamic interaction between psychological (mood, personality, behavior, cognition etc.), social (cultural, familial, socioeconomic, medical, etc.) and biological (genetic, biochemical, etc.) factors [52]. Therefore, treatment should not only focus on the biological aspects of pain (e.g. the spinal pathology and surgery), but also take into account psychosocial aspects. As especially pain catastrophizing has emerged as a robust predictor of CPSP, interventions aimed at reducing this risk factor may improve treatment outcome. CBT is the most frequently used psychological intervention for patients with chronic pain and a recent meta-analysis indicated that it is the most effective treatment for decreasing pain catastrophizing in targeted populations [53].

So far, only a few studies have investigated the impact of a psychological intervention in the perioperative period in patients undergoing spinal fusion [54–57]. Monticone et al. [54] evaluated the effect of CBT for the management of catastrophizing after lumbar fusion surgery. Patients were randomly assigned to exercise plus CBT (*n* = 65) or a control group, consisting of exercises only (n = 65). Exercise plus CBT was found to be superior to the ‘exercise only’ program in reducing disability, dysfunctional thoughts, and pain, and enhancing the quality of life, with effects lasting for at least 1 year after the end of intervention. Abbott et al. [27] offered psychomotor therapy focusing on cognition, behavior, and motor relearning to 53 patients after lumbar fusion surgery and compared outcomes in terms of pain, disability and quality of life to outcomes in 54 patients receiving ‘exercise only’. The psychomotor group reported less disability and higher quality of life until 12 months after the intervention and less pain until 6 months. An important limitation of both studies [27, 54] was that an active control intervention offering more than exercises alone was not included. As exercises were also part of the experimental condition and could be interpreted as ‘usual care’, it cannot be excluded that non-specific factors such as contact time and attention might have played a role. Moreover, treatment expectations might have differed between conditions.

Two more recent studies offered both pre- and postoperative CBT sessions to spinal fusion patients. Lotzke et al. [58] examined the effects of a ﻿person-centred physical therapy rehabilitation program based on a cognitive-behavioral approach consisting of four preoperative and one postoperative session. Fifty-nine patients were randomized to the program and 59 received care as usual. Both groups showed a significant improvement in pain and disability at 6 months’ follow-up, with no differences between the groups. Rolving et al. [55] randomized patients to CBT plus physiotherapy (*n* = 59) or physiotherapy only (*n* = 31). The intervention consisted of 4 preoperative and 2 postoperative CBT sessions. At 1-year follow-up, no significant difference in disability was found between the two groups, but the CBT group achieved a significant reduction in disability earlier than the control group.

It should be noted that none of the above studies preselected patients based on a psychological high-risk profile (i.e. high pain catastrophizing or anxiety/fear) despite the fact that at least some of these interventions were specifically designed to reduce these risk factors. Lotzke et al. speculated that their null finding may have been due to the high degree of variability in fear-avoidance beliefs in their patients [59]. Therefore, they recommended that future studies should evaluate the effects of psychological treatment specifically in patients with a high psychological risk profile for poor outcome.

In line with this recommendation, a crucial aspect of the current study is that we will offer CBT specifically to patients reporting high levels of pain catastrophizing. Another feature, which sets out study protocol apart from most previous studies in this area, is the inclusion of an active control intervention consisting of an educational and progressive exercising program. This allows us to assess the effect of CBT per se and control for non-specific effects such as expectancy, contact time and attention. In addition, starting treatment before surgery may be expected to lead to more profound intervention effects than post-surgical intervention only, because it might decrease early postoperative pain, which is among the most prominent predictive factors for developing CPSP [60]. Finally, we aim to assess the meaningfulness and clinical usefulness of the perioperative CBT intervention by comparing the outcomes of the high PCS/CBT group not only with the control group, but also to the outcomes of the low risk group (i.e. PCS score < 24). This offers the possibility to examine whether CBT can reduce the negative effects of catastrophizing on outcome to the level of improvement one would expect in non-catastrophizing patients.

There are some limitations of our study protocol that should be mentioned. The main limitation is patient’s compliance to the intervention. In fact, very few data exist that analyze the impact and feasibility of CBT in the perioperative period after spinal fusion surgery. Another possible limitation is related to potential differences in levels of catastrophizing between the populations of the two centers. Moreover, the exact proportion of high catastrophizing patients (defined in this study as having a PCS ≥ 24) is not known in advance and could vary between the two centers. Additionally, a potential weakness of our study protocol is related to the control condition, conceived to reduce patient’s expectation bias, augmenting contact time and attention, and therefore reducing non-specific effects on outcome. It is well known in psychological research that expectation is one of the most important non-specific factors that may modulate patients outcomes [61]. However, it is difficult to know if this intervention will control for other non-specific factors that could be present (e.g. patient motivation or the therapeutic relationship between the psychologist and patients during CBT). Additionally, because of the difference in length of sessions between the CBT sessions and the education program (the latter being of a shorter duration) the factor of ‘contact time’ is not perfectly controlled for. On the other hand, the first educational session and post-discharge educational session will be held ‘face to face’ whereas all CBT sessions will be delivered by video teleconference. This ‘in-person attention’ in the two educational sessions might compensate for the shorter contact time in the control group in comparison to the CBT group.

Furthermore, this study can demonstrate efficacy of the CBT intervention for high catastrophizing patients, but it does not assess cost-effectiveness. Although some cost elements are included (medication use, further treatment, employment status), no full cost analyses will be conducted. Moreover, if this study shows a positive effect on pain and disability from perioperative CBT, this will not clarify the optimal dosage of the intervention or the ideal timing. Finally, it cannot clarify whether a PCS score of 24 or higher is the most optimal cut-off for offering patients CBT. Future studies should conduct sensitivity analyses to establish at which level of pain catastrophizing intervention should be offered, to come to an optimal cost-benefit ratio.

In conclusion, the results of this study are expected to provide valuable information that will potentially change clinical practice of lumbar spinal fusion surgery. If our study can demonstrate that perioperative CBT is effective in improving clinical outcome after lumbar spine fusion surgery in high catastrophizing patients, it is highly recommended to perform prescreening to identify this subgroup for which a perioperative psychological treatment will be indicated. If CBT will not prove to be superior and if this study will confirm that high levels of pain catastrophizing have a negative impact on clinical outcome, that might be a reason to be very reluctant in offering these patients a spinal fusion procedure, trying to opt for less invasive treatment options.

